### Ethical Considerations

The consent forms, participants’ information sheets, and all other documentation provided to the participants have received approval from the Ethics Committee of the Affiliated Hospital of Chengdu University of Traditional Chinese Medicine (2024KL-109-01). This clinical trial has been retrospectively registered with the International Traditional Medicine Clinical Trial Registry on November 12, 2024 (ITMCTR 2024000798). All participants will be thoroughly informed about the details of the clinical trial. The consent of participants will be obtained in accordance with the ethical principles and standards based on the Declaration of Helsinki. All participants will have the right to withdraw their consent voluntarily at any time, and all personal information, such as name, gender, and age, will be anonymized or deidentified to ensure that individuals cannot be identified.

Sitting Baduanjin regulates qi, blood, yin and yang, dredges meridians, and adjusts zang-fu organs. It also boasts advantages such as moderate exercise intensity, high safety, and ease of practice. It has been proven safe and effective in previous clinical trials without toxic or side effects. However, acupressure involves external force application, and some patients may experience pain or discomfort. Researchers will make every effort to prevent and treat potential harms arising from this study. If participants experience any discomfort during the research, doctors will conduct evaluations and provide medical treatment accordingly. In the event of adverse events during the clinical trial, a committee of medical experts will assess whether they are related to the trial. For trial-related injuries, researchers will cover the medical treatment costs and provide corresponding economic compensation in accordance with relevant laws and regulations.

## Results

This study was funded in December 2024, with data collection officially initiating on December 15, 2024, and projected to conclude in November 2025. As of the article submission date, 52 participants have been successfully enrolled, and all planned interventions are ongoing. Preliminary analysis of baseline demographic characteristics (eg, age, gender, dialysis duration) has been completed, confirming the balance of key variables across the 3 study groups, while full statistical analysis of intervention effects will be conducted immediately after the completion of all participant interventions and data collection. The trial is expected to be fully completed within 2025, with final study results anticipated to be published in Spring 2026.

## Discussion

### Anticipated Findings

The sitting-style Baduanjin can regulate respiration, adjust the body, and calm the mind. It can gently modulate the functions of internal organs [46]. This form of exercise is relatively less intense, easy to learn and practice, and is not constrained by location. Conversely, acupoint massage stimulates specific acupoints to regulate qi, blood, meridians, and internal organ functions. The procedure is simple and noninvasive, leading to a higher acceptance rate among patients. In addition, establishing community fitness and massage centers can reduce resource burdens and promote intervention applications.

The combination of Baduanjin and acupoint massage as a therapeutic modality within TCM is relatively less popular, and patient acceptance and preferences remain crucial factors that can influence the outcomes of this study. Beyond patient-related factors, the implementation of these TCM therapies also presents inherent complexity: both Baduanjin (the 8-section brocade) and acupoint massage require guidance and execution by individuals with specialized TCM knowledge, which necessitates substantial long-term investment in the training of skilled practitioners. For medical institutions that do not specialize in TCM, adopting and promoting these therapeutic methods thus becomes particularly challenging. Nevertheless, if health care providers and relevant stakeholders can learn and master the core theories and techniques of these TCM interventions, the benefits may extend beyond patients undergoing MHD, potentially benefiting individuals with various other chronic diseases as well.

Notably, this study has several limitations that warrant explicit acknowledgment. First, regarding the intervention duration and sample size: an 8-week intervention period may be insufficient to comprehensively elucidate the long-term therapeutic effects and patient compliance with TCM therapies. This initial time frame was determined based on the study’s research design and resource constraints, which prioritized verifying short-term safety and preliminary efficacy; however, the small sample size further impacts the robustness and generalizability of our results. Second, in terms of study design, the control group only received conventional MHD treatment and care, while the intervention group additionally received either acupoint massage alone or a combined therapy of acupoint massage and seated Qigong. This imbalance in intervention content could easily lead to disparities in attention and participation between the groups, potentially introducing biases such as placebo effects. Furthermore, the combined intervention group lacked a separate control arm (eg, a group receiving only acupoint massage or only seated Qigong), making it impossible to distinguish the independent effects of each intervention component, a gap that may weaken the strength of our evidence. Third, the nature of TCM interventions, which involve active patient participation and a visible practitioner, makes it difficult to implement blinding for both operators and patients, further increasing the risk of bias.

Adding to these limitations, the single-center nature of our sample, recruited from a specific region (eg, North China), may restrict the representativeness of our findings to diverse hemodialysis populations globally. Importantly, TCM acceptance and familiarity vary significantly across different cultural contexts: in non-Chinese settings or regions with limited exposure to TCM, patient adherence to these interventions and the subsequent therapeutic outcomes may differ substantially from those observed in our study. This cultural variability further underscores the need to address generalizability in future research.

To address these limitations and strengthen the evidence base for TCM interventions in MHD care, several future research directions are proposed. First, to improve generalizability, future studies should adopt a multicenter design involving diverse ethnicities, geographic regions, and health care systems. This will help validate whether the effects of Baduanjin and acupoint massage can be replicated across different patient populations and clinical settings. Second, conducting adaptability trials (eg, simplifying the movements of Baduanjin to enhance cultural acceptance or modifying intervention protocols to align with local health care practices) is essential for testing TCM modalities in populations with limited prior TCM exposure. Third, future research should also expand the intervention duration to assess long-term efficacy and compliance, increase the sample size to enhance statistical power, and refine the study design by including separate control arms for individual TCM components (eg, Baduanjin alone and acupoint massage alone). In addition, exploring innovative strategies to minimize bias, such as using objective outcome measures or implementing partial blinding where feasible, will further improve the rigor of future studies. Collectively, these efforts will provide a more robust validation of TCM-based interventions for patients undergoing MHD and support their potential integration into global hemodialysis care.

### Significance for Clinical Practice

The findings of this study could provide effective nonpharmacological interventions to improve frailty status, mental health, and QoL in patients undergoing MHD. This combined intervention can effectively reduce the incidence of complications and readmissions and decrease medical costs and socioeconomic pressures. In addition, it can provide new evidence for integrating TCM nursing measures into chronic disease management.

### Future Research Directions

Several strategies can be implemented to improve the reliability and comprehensiveness of studies on the effects of sit-to-stand Tai Chi combined with acupoint massage in patients undergoing MHD. First, expanding the sample size and study duration by conducting multicenter studies with larger sample sizes and extended intervention periods is essential. This would help to elucidate the long-term effects and improve generalizability accurately. Second, improving the research design by implementing stricter randomization and blinding methods is crucial to minimizing bias and ensuring the validity of the results. In addition, a comprehensive multidimensional evaluation that includes more aspects, such as social support and economic status, should be incorporated to provide a holistic view of the effects of the intervention. Third, optimizing intervention strategies by combining nutritional guidance, psychological counseling, and other relevant methods can improve the effectiveness of the intervention further. By combining these approaches, this study provides robust evidence of the efficacy of this combined TCM therapy in managing frailty in patients undergoing MHD.

### Conclusions

This study protocol presents a randomized controlled trial evaluating the efficacy of sitting Baduanjin combined with acupoint massage in improving frailty among patients undergoing MHD, addressing the gap of insufficient high-quality evidence for combined nonpharmacological interventions in this group. Its core objective is to verify whether this integrated TCM intervention alleviates frailty, enhances physical function, reduces depressive symptoms, and improves QoL, compared to routine care alone or acupoint massage alone. A key strength is the comprehensive evaluation system, integrating the FRAIL scale (primary indicator), objective physical assessments (grip strength and STS-10), and patient-reported outcomes (SDS and SF-36), alongside rigorous design (random allocation, concealed grouping, and blinded data collection and analysis), standardized protocols (8-week and thrice-weekly sessions), and detailed safety monitoring, ensuring feasibility and reliability for patients undergoing MHD. Preliminary results confirm balanced baseline characteristics across groups and good intervention safety (only mild and reversible AEs), supporting clinical applicability. If final results (anticipated Spring 2026) validate efficacy, this study will provide a scientific, low-cost nonpharmacological strategy for MHD-related frailty, enrich evidence for TCM integration into chronic kidney care, and inform clinical guidelines. Future multicenter studies with larger samples and extended follow-up are recommended to verify long-term effects and generalizability.

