### Current Research Gap

Although studies have explored the effects of Baduanjin and acupoint massage on patients undergoing MHD, there are still knowledge gaps. Most studies focus on improving specific indicators, but there is a lack of assessment of the patients’ frailty status. Baduanjin improves muscle function of patients undergoing hemodialysis, reduces systemic inflammation, and enhances skeletal muscle–related indices [34]. Massage relieves lower limb cramps [34] and boosts sleep quality via hot stone therapy [35]. Yet, massage only targets single symptoms (no effects on muscle mass and inflammation); Baduanjin needs nutritional support, covers a few frailty symptoms, and has limited skeletal muscle benefits [34,36]. Their combination could comprehensively address frailty, synergistically protect muscles, and improve frailty via multiple mechanisms. Regarding the effectiveness of combining sitting Baduanjin exercise and acupoint therapy in improving the frailty of patients undergoing MHD, there is also a lack of high-quality evidence.

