### Sample Size Calculation

The sample size calculation formula for the multigroup mean is as follows:

$$n=\varphi^{2}\left(\sum_{i}s_{i}^{2}/g\right)/\left[\sum ({\bar{X}}_{l}-\bar{X}{)}^{2}/(g-1)\right]$$

where n represents the requisite sample size for each group, g represents the number of groups, and Si is the mean (SD) for each group. The values of φ are obtained from tables α, β, ν1, and ν2, with α=.05, β=.1, ν1=2, ν2=∞, and *φ*=2.52. A 2-sided test was used in this study, which stipulates that the test level α=.05, the test efficiency 1-β=.90, and the probability of a type II error is 0.10. The FRAIL scale score was used to calculate the effect size, and the average number of patients in each group, as previously described [37], was as follows: 3.29, 2.67, and 2.58, with SD values of 0.96, 0.87, and 1.02, respectively. These data were entered into the formula to calculate n=34. Considering the shedding rate of 10%, the actual required sample size for the 3 groups was estimated to be 38 per group, totaling 114 patients.

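### The stated 90% power is for a three-group omnibus test and does not cover combined therapy versus massage alone, and the limitations text wrongly says there is no massage-only comparator

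*Protocol article*

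**What the plan says.** **Objective.** The Conclusions describe the aim as testing whether the combined intervention helps "compared to routine care alone or acupoint massage alone". That is two pairwise contrasts.

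**Sample size.** The Sample Size Calculation opens with "The sample size calculation formula for the multigroup mean is as follows". It takes its table value at "α=.05, β=.1, ν1=2, ν2" = ∞, states "A 2-sided test was used in this study" and gives power as "the test efficiency 1-β=.90". The FRAIL inputs come from a cited study: the mean "was as follows: 3.29, 2.67, and 2.58, with SD values of 0.96, 0.87, and 1.02, respectively". The section does not say which mean belongs to which arm. It reports 34 per group, raised to 38 (114 in total) for 10% dropout. No pairwise power is given.

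**Analysis.** Statistical Inference plans a one-way ANOVA after the intervention, followed by least significant difference comparisons if it is significant, or rank-sum tests.

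**Arms.** The Abstract and Intervention Measures describe three arms: usual dialysis care, usual care plus acupoint massage, and usual care plus massage and sitting Baduanjin.

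**Limitations.** Under Anticipated Findings the article says "the combined intervention group lacked a separate control arm (eg, a group receiving only acupoint massage or only seated Qigong"), and concludes that component effects cannot be told apart. The next paragraph lists massage alone among the control arms that future studies should add.

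**The concern.** There are two problems, and both bear on what the trial can conclude about adding Baduanjin to massage.

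First, 90% power is stated once, for a test that asks only whether some arm differs from another. Massage by itself could make that test significant. A reader who takes the 90% as applying to the core objective would expect the combined-versus-massage comparison to be well powered, and nothing in the calculation supports that.

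Second, the limitations text denies the existence of an arm that the trial randomizes to. It therefore disowns the one component contrast that the design can estimate (Baduanjin added to massage) and blurs what it cannot estimate (massage added to Baduanjin, and any interaction of the two). The Introduction offers synergy as rationale: "Their combination could comprehensively address frailty, synergistically protect muscles, and improve frailty via multiple mechanisms". Testing that would need a Baduanjin-only arm.

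**Working it through.** **Inputs, all from the Sample Size Calculation.** Means 3.29, 2.67, 2.58; SDs 0.96, 0.87, 1.02; g = 3; φ = 2.52; two-sided α = 0.05; n = 34 before and 38 after the dropout allowance.

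**1. The plan's own figure.** The formula is n = φ² × (Σs²/g) / [Σ(mean − grand mean)²/(g − 1)].
- Σs²/g = (0.9216 + 0.7569 + 1.0404)/3 = 0.9063, so the pooled SD is 0.952.
- Grand mean 2.8467. Squared deviations 0.1965 + 0.0312 + 0.0711 = 0.2989; divided by 2, 0.1494.
- n = 6.3504 × 0.9063 / 0.1494 = 38.5, so 39 per group. The stated 34 is not reproduced.
- Omnibus power from the noncentral F with 2 and 3n − 3 degrees of freedom: 84.8% at 34 and 88.8% at 38. With ν2 = ∞, as in the plan: 86.0% and 89.7%.
- The inflation step itself is right: 34/0.9 = 37.8, so 38.

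**2. Where the omnibus signal comes from.** Split the 0.2989 into two orthogonal parts:
- 3.29 against the average of the other two (2.625): (0.665)² × 2/3 = 0.2948, or 98.6%.
- 2.67 against 2.58: (0.09)²/2 = 0.0041, or 1.4%.

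**3. Pairwise power.** Assumption: 3.29 is control and the other two means are the two active arms, in either order. The standard error of a difference at n = 34 is √(2 × 0.9063/34) = 0.231. Noncentral t, 99 error df, two-sided 0.05:

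| Difference | What it is | Power, n = 34 | Power, n = 38 |
|---|---|---|---|
| 0.71 | control vs the arm at 2.58 | 86% | 90% |
| 0.62 | control vs the arm at 2.67 | 76% | 80% |
| 0.09 | combined vs massage | 6.7% | 6.9% |

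A simulation (100,000 runs) that tests the pair only after a significant ANOVA gives 6.6% at n = 34 and 6.8% at n = 38 for the 0.09 difference.

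**4. Range for combined versus massage.** The 0.09 depends on the arm assumption, so other differences are shown at n = 34 with the same SD:
- 0.3 points: power about 25%.
- 0.5 points: power about 57%.
- 0.65 points: power about 80%.

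The 95% confidence interval half-width does not depend on the assumed difference: 1.984 × 0.231 = 0.46 points at n = 34 (0.43 at n = 38).

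**5. The limitations text against the design.** The Abstract and the Acupoint Massage Group section describe a massage-only arm. The Conclusions use it as a comparator. The limitations paragraph itself, just before the disputed sentence, says that patients received either massage alone or the combined therapy. The statement that no massage-only group exists contradicts all of these.

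What the three arms can estimate:
- massage versus control: the effect of massage;
- combined versus massage: the effect of adding Baduanjin to massage;
- combined versus control: the effect of the package.

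Without a Baduanjin-only arm, they cannot estimate the effect of adding massage to Baduanjin, or whether the combination exceeds the sum of its parts.

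**The case against.** **The 7% rests on an unseen source.** The means are unlabelled, come from a cited study, and may not describe the same interventions. This stands, so 7% is a conditional figure and needs the range beside it. The ordering is nonetheless reasonable: a higher FRAIL score is worse, and the article lists control first. Exchanging the other two labels leaves the gap at 0.09. Only if 3.29 belonged to an active arm would combined versus massage reach 76% to 86%.

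**A difference of 0.09 is not a clinically important difference.** True, and the article gives none. At 0.5 points about 57 per arm would be needed for 80% power and 77 for 90%. A reader might infer from 0.09 that thousands of patients per arm are required; the documents do not support using that one value as the target.

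**Combined versus massage is one of two comparisons.** Correct. A reader might infer that the trial is underpowered for its whole core objective. It is not: under the same assumption, an active arm against control has 76% to 86% power at 34 per group.

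**The plan does test pairs.** Least significant difference testing after ANOVA addresses combined versus massage directly, and nothing in the article says that a significant overall F will be taken as proof of added benefit. So misreading is a risk to guard against, not a stated intention.

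**Some of this is disclosed.** The limitations call the sample small, and the future directions ask for a Baduanjin-alone arm. The synergy sentence is background, not a stated objective. But a general remark on sample size does not tell readers which comparison is weak, and the disclosure about arms is itself wrong.

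**Conclusion.** The point holds in two parts.

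The misstatement about the massage-only arm is certain and needs no assumption. Only a Baduanjin-only arm is missing.

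It is equally certain that the 90% applies to an omnibus test, that no pairwise power is given, and that the article's inputs give 39 rather than 34 per group, with about 85% omnibus power at 34. How weak combined versus massage is depends on assumptions: about 7% power if the unlabelled means map onto the arms in the natural order, and about 25% to 57% for assumed differences of 0.3 to 0.5 points with SD 0.952. Across that range it falls well short of 90%, and the interval will extend about 0.46 points either side of the estimate.

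A reader might go further and conclude that the primary analysis must be changed to combined versus control. The documents do not require that. It would alter the primary analysis of a trial with 52 patients already enrolled, and it would put most weight on the contrast most exposed to the attention imbalance that the article acknowledges.

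**What to change.** 1. **Anticipated Findings.** Correct the limitations sentence and the matching line on future control arms. Say that combined versus massage estimates the added effect of Baduanjin, and that without a Baduanjin-only arm neither the effect of adding massage to Baduanjin nor any synergy can be estimated.
2. **Sample Size Calculation.** Say that the power is for the three-group omnibus test, and reconcile 34 and 90% with the formula. Label the means by arm, or state the mapping as an assumption. Add pairwise power with a range for combined versus massage, for example at 0.09, 0.3 and 0.5 points.
3. **Analysis and reporting.** Report combined versus massage as an estimated difference with its 95% confidence interval. State beforehand that a significant overall F does not show added benefit of Baduanjin, and that a non-significant pairwise result does not show its absence.

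Naming combined versus control as the sole primary contrast is optional.

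**Cost.** Changes of text and a narrower claim, with no extra patients for these changes. The article says that the analysis of intervention effects will follow completion of data collection, so the wording can be settled before then.
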